**Methods:**

This is a prospective longitudinal cohort study of adult (≥18 years) acute medical hospital admissions with nested health economic and situation analysis in four hospitals: 1) Queen Elizabeth Central Hospital, Blantyre, Malawi; 2) Chiradzulu District Hospital, Malawi; 3) Hai District Hospital, Boma Ng’ombe, Tanzania; 4) Muhimbili National Hospital, Dar-es-Salaam, Tanzania. Follow-up duration will be 90 days from hospital admission. We will use consecutive recruitment within 24 hours of emergency presentation and stratified recruitment across four sites. We will use point-of-care tests to refine estimates of disease pathology. We will conduct qualitative interviews with patients, caregivers, healthcare providers and policymakers; focus group discussions with patients and caregivers, and observations of hospital care pathways.

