### Objectives

The primary objectives of this mixed methods (clinical, health economics and qualitative) study are:

*Clinical:* Determine the prevalence of multimorbid disease in adults admitted to hospital with acute medical conditions in Malawi and Tanzania.

*Health Economic:* Measure economic costs incurred and changes in health-related quality of life between admission and 90 days post admission.

*Situation analysis:* Describe current care for multimorbidity, enabling and hindering factors to the delivery of patient centred care.

We aim to use the findings to inform the development and design of a randomised controlled trial.

The secondary objectives are:

*Clinical:*

1.Measure prevalence of important pre-selected individual conditions, including chronic non-communicable (hypertension, diabetes mellitus and chronic kidney disease) and communicable (HIV infection) conditions.2.Measure hospital readmission rate 30 and 90 days after admission.3.Measure survival 30 and 90 days after admission.4.Measure a composite of readmission free survival 30 and 90 days after admission.5.Measure markers of disease control 90 days after admission.6.Measure the rate of end-organ damage (such as cerebrovascular accident and myocardial infarction).

*Health Economic:*

1.Disaggregate economic costs from patient and health system perspectives and sub-analyse according to the presence of multimorbidity and other socio-economic factors.2.Model how patients with different multimorbidity incur costs as they pass through the health system.3.Analyse changes in Health-related Quality of Life according to presence of different diseases.4.Estimate the potential cost-effectiveness of a selected intervention to improve diagnosis and treatment for people with multimorbidity.

*Situation Analysis:*

1.Describe healthcare pathways for adults during and after acute medical admission using structured observational data during patient admission.2.Qualitatively describe (i) patients’ level of health literacy related to their own conditions and (ii) healthcare engagement for patients with multimorbidity using key-informant interviews.

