### Participants

**
*Phase 1 A: Prospective longitudinal cohort study*.** Patients will be screened for enrolment at the primary point of entry for hospital admission. Cohort study participants will be consecutively recruited within 24 hours of emergency presentation, and stratified recruitment across four sites. Eligibility criteria are as follows:

Inclusion:

1.Adult patients (aged ≥18 years).2.Decision to admit to hospital.3.Physician diagnosis of an acute medical disorder.4.Residence within the study catchment area (predefined for each hospital site).5.Contactable on discharge by phone (either directly or through a carer).

Exclusion:

1.Pregnancy (other research groups are specifically addressing this).2.Planned medical admission.3.Detainees or prisoners.4.Admission for primary trauma, obstetric or gynaecological condition.5.Patient or carer declines consent to take part.

The study procedures and schedule for follow-up are described in
Table 1.

**Table 1. T1:** Study procedures and sampling schedule.

Study Visit	A	B	C	D	E	F	G
Day post admission	0	2	5	7	Discharge	30	90
Deferred consent	x						
Consent (verbal)	x	x	x	x	x		x
Consent (written)	3	3	3				
Vital signs (including blood pressure)	x	x	x	x	x		x
Medical history, function (including grip strength) and outcome assessment	x					4	x
Screen for Adverse Events (AEs)	x	x	x	x	x		x
HIV POC *	x						x
Where HIV, VL, urinary LAM, serum CrAg *	x						1
Blood glucose POC	x	x	x	x			x
HBA1c POC	x						x
Creatinine POC	x						x
Urinary dipstick	x						x
Serum save 5mL)	x						x
Situation analysis	x	x	x	x	x		x
Patient and health system costs					x	x	x
EQ5D questionnaire	x					x	x
Qualitative interviews					x		x

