### Variables

**
*Phase 1 A: Prospective longitudinal cohort study*.** The main outcome is to define the characteristics of multimorbidity. We will employ enhanced point of care test (POC) diagnostics for patients admitted to the study to determine the prevalence of multimorbid diseases of interest (specifically HIV, hypertension, diabetes and chronic kidney disease). All POCs used in the study are CE marked and commercially available. We will make the results of these tests available to treating healthcare providers using a standardised proforma. No treatment recommendation will be provided with this information and clinicians will be able to interpret and use this information independently. Structured data extraction of clinical information (including potential predictors of patient outcomes) will be performed at intervals (described in
Table 1 from patient records.

**
*Phase 1 B: Health economic evaluation*.** To explore the impact of socioeconomic status (SES) on patient costs, clinical outcomes and health-related quality of life (HRQoL) we will calculate wealth scores and use these to assign all clinical cohort study participants to SES quintiles. For participants randomised to the health economic study, we will collect data on patient costs at admission (in person), discharge (in person), 30 and 90 days post discharge (in person or by telephone). Health system costs for patients in the cohort study will be modelled using top down and bottom up costing methods. HRQoL will be estimated in quality adjusted life years (QALYs).

**
*Phase 1 C: Situation analysis*
** In depth interviews (IDI) and focus group discussions (FGD) with patients recruited to the cohort study, and their care givers will be conducted to understand their experiences, preferences, and priorities, including level of health literacy and engagement with healthcare providers for long term management of chronic conditions. Exploration of detailed experiences from patients and carers will provide specific concrete examples of their expectations, and any concerns they have, as well as their priorities and perceptions of how the hospital currently manages acute medical patients with multimorbidity, problems and how best to address them.

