### Analysis

**
*Phase 1 A: Prospective longitudinal cohort study - quantitative statistical analysis*.** We will report the study in accordance with STROBE guidelines. A CONSORT diagram will summarise participant enrolment and follow-up. We will report descriptive statistics, including N (sample size of analysis population), n (sample size of analysis population without missing values). For continuous data we will report the mean and standard deviation for normally distributed data, or median and interquartile range for data that are not normally distributed. The proportion of observed levels will be reported for all binary and categorical measures alongside corresponding exact, binomial exact 95% confidence intervals (CIs) for proportions when appropriate. Results will be disaggregated by sex. Where appropriate, we will use multiple imputations using chained equations for missing data.

Will provide in-depth baseline epidemiologic and clinical management data across the different sites. Similarities and differences across sites will be recorded. Analysis will include evaluation of the association between clinical management and patient outcomes. Univariate and multivariate strength of association between variables and patient outcomes will be tested by logistic regression modelling.

Prevalences will be given as a proportion with 95% confidence intervals of the population estimate. Combinations of more than one will be assessed for their “joint prevalence” in order to understand multimorbidity disease clusters.

**
*Phase 1B: Health economic*.** Principle components analysis (PCA) will be used to construct wealth scores using individuals’ asset and other data, and wealth quintiles in the study population. Additionally, participants will be assigned to quintiles in reference to most recent DHS survey, allowing socioeconomic assessment of the study population relative to the national population.

Patient costs will be estimated for each individual patient including any costs incurred by their guardians in accompanying them to hospital or subsequent health care visits. Indirect costs (

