*e.g.*, lost time for paid or unpaid work, including housework) will be estimated based on the number of days of reported inability to work multiplied by the pre-disease wage given by patients during their baseline interview. The patient pathway model will be parameterised with unit costs and used to estimate individual patient and health system costs for a set of the most frequently observed multimorbidity combinations and patient types. Capital costs extending beyond one year will be annualised over their expected lifespan. Results will be presented as means and 95% confidence intervals. Deterministic and probabilistic sensitivity analyses will be conducted to test the robustness of the results. Multiple logistic regression will be used to compare patient costs by multimorbid condition(s) and wealth quintile to identify any significant differences. Additionally, we will examine the relationship between patient costs and age and sex. Change in HRQoL, expressed as QALYs, between admission, day 30 and day 90 interviews will be estimated using the area under the curve method. QALYs will be calculated according to the most relevant available tariff based on both geographical proximity and economic context. In our study we will use Uganda’s tariff for Tanzania, and Zimbabwe’s tariff for Malawi. Updated tariffs will be used if these become available before the analysis. The QALY calculations will also consider mortality during follow-up by attributing the lowest value from each value set (which corresponds to death), from the date of death until the end of the follow-up period. Missing patient cost or HRQoL data will be imputed using multiple chained imputations modelling with a predictive mean matching algorithm and relevant baseline variables.

Health economic analysis will be performed in Stata v15.4 and Excel.

**
*Phase 1 C: Situation analysis*.** Transcription and translation will be performed in line with local standard procedures. For accuracy, during the first 10 transcriptions a researcher will read the transcribed interviews and focus groups while listening to the audio recordings, and then check translations. Further checks will depend on the quality of these initial evaluations.

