## Limitations

There are a number of limitations with this study, which we have attempted to mitigate. First, there are a limited number of sites in two countries. In order to generate broadly generalisable results, the chosen sites reflect a mix of tertiary / referral hospitals and district hospitals in each country. Second, we have decided to systematically screen for four conditions (HIV, hypertension, diabetes and CKD) using point-of-care diagnostics. This may miss multimorbidity from other chronic conditions, which require additional infrastructure to confirm diagnoses (such as clinical imaging or enhanced laboratories), but we will collect clinical data on all diagnosed chronic conditions. A recent systematic review indicates a high burden of disease from these four conditions among hospitals patients, which can importantly be diagnosed using available point-of-care tools
^
24
^. Third, CKD diagnoses require evidence of chronicity of disease at three months and therefore data in this condition is prone to survivorship bias. Fourth, EQ5D-5L data and resulting QALY estimates may not reflect the most accurate picture of HRQoL in our study context. However, through our eCRF, we will collect rich clinical data with additional scales (such as the Patient Health Questionnaire-9 [PHQ-9] screening tool for depression
^
34
^; and clinical frailty scale
^
35
^ to explore the possible limitations and interrelationships. Fifth, our planned situation analysis will provide a cross-sectional picture of the health system at the time of the study, which is not able to incorporate the dynamic and adaptive nature of health systems. However, the MultiLink consortium includes researchers from each country and site, with a rich understanding of the context.

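### CKD not documented before admission can be labelled only in patients who reach day 90, yet QALYs and costs counted from admission are compared by that label

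*Protocol article*

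**What the plan says.** CKD is one of four conditions that the cohort is designed to detect (Variables, Phase 1 A): "specifically HIV, hypertension, diabetes and chronic kidney disease". The Limitations section adds the condition that matters here: "CKD diagnoses require evidence of chronicity of disease at three months and therefore data in this condition is prone to survivorship bias". In Table 1 (Participants), the row "Creatinine POC" is marked at day 0 and day 90 only, and so is the urinary dipstick row. The abstract's Methods fix the outcome window: "Follow-up duration will be 90 days from hospital admission".

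Disease status is then used to form comparison groups:

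- Health economic secondary objective 3: "Analyse changes in Health-related Quality of Life according to presence of different diseases".
- Health economic secondary objective 1 has costs disaggregated and then "sub-analyse according to the presence of multimorbidity and other socio-economic factors".
- Analysis, Phase 1B: "Multiple logistic regression will be used to compare patient costs by multimorbid condition(s) and wealth quintile". The same section carries deaths into the QALYs by assigning the lowest value of the tariff from the date of death to the end of follow-up.
- Analysis, Phase 1 A: "Univariate and multivariate strength of association between variables and patient outcomes will be tested by logistic regression modelling". The variables are not named, so disease status may or may not be among them.

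The article does not say how a patient who dies before day 90 is classified for CKD, or for any multimorbidity combination that depends on CKD.

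**The concern.** For CKD without earlier documentation, membership of the exposed group depends on surviving the period over which the outcome is counted. A patient with HIV and a raised creatinine at admission who dies in the first week has no confirmed CKD. That patient must be counted as non-CKD, set aside, or given an imputed status. The first option moves deaths from the CKD group to the comparator. Setting aside only the unconfirmed cases still leaves a newly confirmed CKD group without deaths.

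This differs from CKD prevalence being underestimated, which the Limitations section already implies. A corrected prevalence figure would not repair a contrast whose groups were formed by survival. The results are meant to inform intervention design, and the Sample size section singles out CKD as the condition whose inclusion the cohort must decide. A CKD group that appears to do better than it does could mislead that decision.

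**Working it through.** The article gives no figure for this contrast, so there is none to reproduce. One input comes from the document: CKD prevalence of 7.7% (Introduction). The rest are assumptions chosen for illustration. All results are expected proportions, without sampling error.

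**1. CKD versus non-CKD, early deaths counted as non-CKD**

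Assumed: 90-day mortality mC = 0.35 with CKD and m0 = 0.25 without; attendance a = 0.9 among survivors; a share d of CKD documented before admission.

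- True OR = (0.35/0.65)/(0.25/0.75) = 1.62.
- Labelled CKD, per true CKD patient = d + (1−d)(1−mC)a. Deaths among them = d·mC.
- At d = 0.3: labelled = 0.3 + 0.7×0.65×0.9 = 0.7095; deaths = 0.105; mortality = 14.8%.
- Comparator size = 0.923 + 0.077×(1−0.7095) = 0.9454. Deaths = 0.923×0.25 + 0.077×0.7×0.35 = 0.2496. Mortality = 26.4%.
- Observed OR = (0.105/0.6045)/(0.2496/0.6958) = **0.48**.

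| Documented share d | Observed OR (true 1.62) |
|---|---|
| 10% | 0.16 |
| 30% | 0.48 |
| 50% | 0.81 |
| 62% | 1.00 |
| 100% | 1.62 |

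With no true difference (25% in both groups) and d = 0.3, the observed OR is 0.31.

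**2. Unconfirmed early deaths dropped instead (d = 0.3)**

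- Only the unconfirmed CKD deaths dropped: comparator deaths = 0.23075 and survivors = 0.6958, so OR = 0.1737/0.3317 = 0.52.
- 40% of non-CKD deaths also dropped, because their admission creatinine was raised: OR = 0.87. At 50%: OR = 1.05. Both remain well below 1.62.

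**3. Sensitivity on the risk-ratio scale**

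With full attendance, non-CKD mortality of 20%, a true ratio of 2 and early deaths counted as non-CKD, the observed ratio is 0.65, 1.17 and 1.61 when 25%, 50% and 75% of CKD is identifiable before death. The direction reverses below about 41%. For mortality of 10% to 30% and true ratios of 1.5 to 3, that threshold runs from 6% to 66%.

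**4. QALYs, with no CKD documented beforehand and full attendance**

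Assumed: survivors' utility rises from 0.5 to 0.8, deaths occur at day 15 with utility 0.4 until then and 0 after, non-CKD mortality is 20% and CKD mortality 40%.

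- Survivor QALY = 0.65×90/365 = 0.1603. Decedent QALY = 0.4×15/365 = 0.0164.
- True means: CKD 0.6×0.1603 + 0.4×0.0164 = 0.1027; non-CKD 0.8×0.1603 + 0.2×0.0164 = 0.1315. Difference = −0.029.
- Observed: CKD 0.1603. Non-CKD (0.923×0.1315 + 0.0308×0.0164)/0.9538 = 0.1278, where 0.0308 = 0.077×0.4. Difference = **+0.033**.

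The sign reversed in every such scenario tried (10% to 30% mortality, ratios 1.5 and 2, utility decrement 0 or 0.05). All of them assume that no CKD was documented beforehand.

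**5. Multimorbid versus not**

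Taking the article's prevalences (HIV 36.4%, hypertension 24.7%, diabetes 11.9%, CKD 7.7%) as independent, 17.49% have two or more conditions. Of all patients, 0.077×0.4369 = 3.36% are multimorbid only because of CKD, which is about 19% of the multimorbid group. Assume mortality of 20% without and 30% with multimorbidity, and no CKD documented beforehand:

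- Deaths that lose the label = 0.0336×0.30 = 0.0101.
- Observed multimorbid mortality = (0.0525−0.0101)/(0.1749−0.0101) = 25.7%.
- Observed comparator mortality = (0.1650+0.0101)/(0.8251+0.0101) = 21.0%.
- Ratio = **1.23**, against a true 1.5.

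On the same basis, true ratios of 1.10, 1.25 and 2.0 are observed as 0.90, 1.02 and 1.64.

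**The case against.** The strongest reply is that the article fixes no bad rule. It never says that early deaths become non-CKD. It reports the number without missing values separately, plans multiple imputation where appropriate, and may leave classification to a full protocol or SAP that is not shown. This stands in part: where early deaths go is unknown, and a reader who infers that the comparator absorbs them goes beyond the text. But the article does state both a diagnosis that depends on reaching three months and comparisons that use it. Step 2 shows that dropping unconfirmed patients does not reliably remove the bias. Imputation could help, but newly confirmed status is never observed in an early death, so the model must extrapolate from survivors.

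Three further objections stand. First, previously known CKD needs no day-90 visit: past medical history and all diagnosed chronic conditions are recorded. The problem is confined to CKD without earlier documentation. Second, no mortality comparison by CKD or multimorbidity is named. The clinical objectives only measure survival and readmission, and the regression refers to unspecified variables. The comparisons stated by disease or multimorbidity are HRQoL and costs; the odds ratios above show the mechanism, not a planned analysis. Third, a reader might infer that the overall multimorbidity contrast reverses. Step 5 shows mainly attenuation, with reversal for weak true effects.

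The survivorship bias is also openly disclosed. However, the disclosure is confined to CKD data, is not carried into the group comparisons, and has no mitigation beside it, although the section opens by saying that mitigation was attempted.

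**Conclusion.** The point holds for CKD-specific contrasts, and for multimorbidity clusters containing CKD, when the outcome runs from admission. The CKD label depends partly on survival, the QALYs count deaths, and the article states no safeguard. If early deaths are counted as non-CKD, or only unconfirmed cases are dropped, such contrasts shift towards CKD looking protective and can reverse when little CKD is documented beforehand. In the main illustration, reversal occurs below about 62% documented. That size rests on assumed mortality, attendance and documentation; only the prevalences come from the article.

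Cost contrasts are exposed to the same misclassification, because early deaths contribute short stays, but their direction and size were not calculated. The overall multimorbidity contrast is mainly attenuated. The documents do not support saying that CKD can be confirmed only at day 90, that early deaths are in fact placed in the comparator, or that a mortality comparison by CKD is planned.

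**What to change.** For QALYs, costs and any outcome comparison by disease or multimorbidity, classify kidney status from information available at admission, in three levels: documented CKD; abnormal admission eGFR or dipstick with undetermined chronicity; neither. Keep the undetermined level out of the no-CKD reference group, and define multimorbidity for these comparisons in the same way. Use day-90-confirmed CKD for the prevalence estimate and for analyses that start at day 90, such as the longer-term telephone outcomes mentioned under Table 1. Add a sensitivity analysis with bounds, or with CKD status imputed in early deaths, and state how patients who die before day 90 are handled.

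The cost is one analysis rule using the day-0 creatinine, dipstick and history already scheduled for collection. The Study status section says that analysis has not been performed and code is still being developed, so the rule can be set now. The downside is that the undetermined group mixes acute and chronic kidney disease and must be labelled accordingly.

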## Phase 2 methods: Intervention development

We will share the information and learning from clinical, health economic and qualitative situation analysis and use relevant national treatment guidelines to develop a set of diagnostic and treatment algorithms which seek to optimise care for people with multimorbidity. Group discussions will be held at all recruitment sites to ensure we have accurately understood and synthesized the issues identified through situation analysis, and to explore stakeholder perceptions on the feasibility and desirability of our proposed intervention for the RCT phase.

We will work with stakeholders (frontline healthcare workers, hospital managers and patients/their representatives) in both countries to explain our proposed intervention and get their feedback on practicality, risks and possible improvements. This will consider quantitative resourcing requirements (
*e.g.*, in relation to staffing levels and bed space) as well as feedback from healthcare workers and patients on practical and emotive considerations.

The preferred intervention package will then be tested under Phase 3 (cRCT) under a separate protocol.

